# Qatar Diabetes Mobile Application Trial (QDMAT): an open-label randomised controlled trial to examine the impact of using a mobile application to improve diabetes care in type 2 diabetes mellitus—a study protocol

**DOI:** 10.1186/s13063-022-06334-5

**Published:** 2022-06-16

**Keywords:** Type 2 diabetes mellitus, Self-management, Mobile health, Lifestyle change, Clinical trial

## Abstract

**Background:**

Mobile health (mHealth) is increasingly advocated for diabetes management. It is unclear if mobile applications are effective in improving glycaemic control, clinical outcomes, quality of life and overall patient satisfaction in patients with type 2 diabetes (T2DM). A new mobile application was specifically built for people with T2DM with the help of the local expertise. The objective of the study was to evaluate the effectiveness of the mobile app.

**Methods:**

The planned study is an ongoing open-label randomised controlled trial in which adults living with T2DM treated with insulin will be randomised 1:1 to the use of this diabetes application versus current standard care. The primary outcome will be the difference in mean HbA1c from baseline to 6 months. Other outcome measures include anthropometric measures, hypoglycaemic events, medication adjustments, number of clinical interactions and missed appointments and patient perceptions of their disease and diabetes self-management. The study will randomise 180 subjects for assessment of the primary outcome.

**Discussion:**

We hypothesise that the diabetes-specific mobile application will improve glycaemic control, increase patient empowerment for self-management of diabetes and improve interaction between patients and healthcare providers. If the Qatar Diabetes Mobile Application Trial (QDMAT) demonstrates this, it will inform clinical services for the future self-management of T2DM.

**Trial registration:**

ClinicalTrials.gov Identifier: NCT03998267. Registered on 26 June 2019

## Administrative information

Note: the numbers in curly brackets in this protocol refer to SPIRIT checklist item numbers. The order of the items has been modified to group similar items (see http://www.equator-network.org/reporting-guidelines/spirit-2727-statement-defining-standard-protocol-items-for-clinical-trials/).

## Introduction

### Background and rationale {6a}

Type 2 diabetes Mellitus (T2DM) is a chronic disease associated with serious micro- and macro-vascular complications that reduce quality of life and longevity with adverse social and economic consequences [1]. T2DM prevalence is increasing globally but at a more rapid pace in the Middle East and North Africa (MENA) region, and particularly in Arab countries in the Gulf Cooperation Council [2, 3]. T2DM management is focused around glycaemic, blood pressure and lipid control [4]. However, even with well-established and enhanced clinical services, achieving appropriate clinical and biochemical targets to prevent, diminish and reverse diabetes complications, is challenging [5]. This is because T2DM management is a complex process requiring integrated clinical care and self-management.

Given the brevity of clinical encounters because of lack of capacity to cater for the increasing number of patients with T2DM, self-management is vital to T2DM care [6]. T2DM self-management requires comprehensive patient education on lifestyle, behavioural change, medication management and adherence and dealing with specific circumstances such as acute illness (“sick day” rules), supported by the clinical diabetes management team. Self-monitoring generally includes blood glucose measurements for people with T2DM treated with insulin but may also include blood pressure, body weight, physical activity and dietary intake measures. As T2DM progresses, there is a need for treatment intensification and the introduction of insulin, which is associated with hypoglycaemia and undesirable weight gain [4, 7]. People with T2DM treated with insulin require more frequent support and healthcare contact especially when insulin is initiated or insulin dose is altered. Providing this through the standard clinic setting is challenging.

T2DM management is increasingly supported by mobile health (mHealth) technologies [8–10] allowing self-monitoring and peer interaction as well as remote monitoring, education, coaching [11] and support by healthcare professionals [12–14]. Furthermore, mHealth allows more convenient remote interaction between the patient and healthcare providers. Thus, mHealth approaches could not only improve T2DM self-management but also allow a more efficient and cost-effective platform for managing the growing number of patients.

Several types of smartphone apps exist for T2DM self-management [15]. The characteristics of these apps, including increased accessibility to educational resources and self-management strategies, more frequent physical and emotional symptom tracking and increased access to peer support, are strengths in benefiting patients' self-management. Based on systematic review, mobile phone-based interventions with clinical feedback improve glycaemic control (HBA1c) compared to standard care or other non-mHealth approaches by as much as 0.8% (9 mmol/mol) for people with T2DM and 0.3% (3 mmol/mol) for people with type 1 DM (T1DM), at least in the short-term (12 months) [13]. The effectiveness of mHealth apps is likely to be influenced by local culture and population mix. There are few studies of mHealth using mobile apps in Arab countries. mHealth interventions are likely to be well-received in Arab countries where the majority of patients with DM are young [16, 17] and likely to be more proficient with mobile app use. Also, digital platforms are increasingly used to seek health information by patients, demonstrating a wish to embrace digital technology for healthcare [18]. In a pilot study of 20 patients with T2DM in Saudi Arabia, there was a reduction in HBA1c from 8.8% (7 mmol/mol) to 7.9% (63 mmol/mol) in the mHealth intervention group compared to a change from 8.6% (70 mmol/mol) to 8.7% (72 mmol/mol) in the control group [19]. The mean diabetes knowledge for the intervention group rose significantly from 46.2 to 61.1% in 6 months using an adapted Diabetes Knowledge questionnaire. The control group also showed slight increase from 43.7 to 46.1% [19].

Recently, the Droobi app (https://en.droobihealth.com/) was co-created by healthcare professionals, patients and computer scientists as a platform for DM management for the Arabic speaking population catering for shared language and sociocultural factors [20]. The Droobi app provides an avenue for more frequent and personalised contact amongst patients, diabetes educators, dietitians and physicians. Rather than focusing on a single functionality as found in many diabetes related mobile apps [15], the Droobi app has three key functionalities: (i) self-management through recording of key measures such as capillary glucose readings, diet, and activity; (ii) education platform for lifestyle support and (iii) real-time interaction with healthcare professionals (physicians, diabetes educators, and dietitians). The aim of the Qatar Diabetes Mobile Application Trial (QDMAT) is to examine the impact of including the Droobi app in diabetes care on diabetes outcomes compared to standard diabetes care. The clinical trial is conducted in Qatar which benefits from a multinational Arab population with a high prevalence of chronic diseases including diabetes [16, 21].

### Objectives {7}

QDMAT will examine the hypothesis that the use of the Droobi diabetes management mobile app platform results in better glycaemic control in patients with T2DM compared to standard care. Secondary outcomes of interest include other key diabetes outcome measures (e.g. blood pressure) and diabetes self-care.

### Trial design {8}

QDMAT is an ongoing open-label parallel group randomised clinical trial. Participants with T2DM who are treated with insulin will be randomised with a 1:1 ratio into an intervention arm and standard care arm. Participants in the intervention arm will receive care through the Droobi mobile app in addition to their standard care. Participants in the control group will receive the usual DM care based on national and international DM care guidelines [22, 23].

A diabetes population comparator group will be used to examine the natural progression of diabetes and its treatment outside the randomised controlled trial. This population will contextualise and determine the effectiveness of the trial arms compared to a non-randomised population.

## Methods: participants, interventions and outcomes

### Study setting {9}

QDMAT is conducted in a secondary care diabetes care setting at Hamad Medical Corporation (HMC), the largest national public medical care provider in Qatar.

### Eligibility criteria {10}

#### Inclusion criteria

The following will be included in QDMAT:Adults with T2DM (based on clinical records);18–60 years of age;Uncontrolled DM with HBA1c ≥ 8.5% (69 mmol/mol);Insulin treated T2DM;Arabic or English language speaking and able to read and write in one of these languages;Possession of a smart mobile phone and willing to use a smart phone app;Able to communicate via chat with the mobile app team through the app as evidenced by at least weekly use of any of the social media apps;Willing to utilise a mobile application for DM management.

#### Exclusion criteria

The following will be excluded in QDMAT—those with:A recent history (3 months) of stroke or myocardial infarction;Proliferative diabetic retinopathy;Any acute illness in the past 2 weeks;Any planned absence for more than 3 months;End-stage renal disease requiring renal replacement therapy;Hypoglycaemia unawareness;More than one episode of severe hypoglycaemia in the previous 6 months;Female gender who are planning for pregnancy in the coming 6 months;Visual impairment preventing use of the app.

The inclusion criteria aim at involving patients with type 2 diabetes who are uncontrolled on insulin therapy who need closer monitoring and management. Having a phone with the technical ability to support the app in addition to the participant’s willingness to use the technology are key for testing the intervention.

The key exclusion criteria aim at reducing the risk of severe hypoglycaemia and potential deterioration of diabetes complications with short-term glycaemic improvement (e.g. proliferative retinopathy may be worsened by rapid improvements in glycaemic control). An acute illness may result in acute blood glucose fluctuations. Recent stroke or myocardial infarction may render the participant at risk of hypoglycaemia.

### Who will take informed consent? {26a}

All written informed consent will be taken by trained clinical research personnel listed on the trial delegation log. A two-stepped process was adopted for the study to cater for potential participants without recent biochemical investigations and to aid rapid study recruitment. Potential participants will be consented initially to screen for study eligibility with up-to-date biochemical measures. If eligible for the study, participants will be consented after more detailed explanation of the research and randomised into the randomised clinical trial.

### Additional consent provisions for collection and use of participant data and biological specimens {26b}

No biological specimens for research purposes will be collected as part of the study.

## Interventions

### Explanation for the choice of comparators {6b}

The comparator group with be standard diabetes care following national and international guidelines [22, 23]. Since in clinical trials, the comparator group often benefits from improved outcomes through trial participation, as part of the study, an observational matched diabetes population comparator group will also be examined using data from electronic medical records. This will contextualise and determine the effectiveness of the trial arms compared to a non-randomised population.

### Intervention description {11a}

#### The Droobi app

The Droobi app is provided to participants at no cost. The app is currently available in both Arabic and English languages. It allows participants to enter self-measured blood glucose readings, weight, food entries, communicate with their physician, diabetes educator and dietitian through a chat function, together with reviewing their medication plan and the educational curriculum on diabetes. Figure 1 shows the app’s patient interface. Participants are alerted when they do not enter their blood glucose readings and when their medication plan or blood glucose monitoring frequency has been adjusted.

**Fig. 1 Fig1:**
[figure not shown]
The Droobi app. **a** Home/landing page. **b** Blood glucose level entry. **c** Body weight entry. **d** Food portions entry. **e** Food photo entry. **f** Activity entry. **g** Toolbox educational curriculum. **h** Lesson 1 from the curriculum

Healthcare providers access through a Droobi portal (Fig. 2). Here, they can review the list of participants and can have an overview of active participants and any triggers highlighted (i.e. low or high blood glucose entries) in order to prioritise care. Also, individual participants blood glucose readings and food entries may be reviewed and their medications and frequency of monitoring adjusted as needed together during chats with the assigned healthcare providers. Educators send a report for the assigned physician in order to adjust participant’s medication plan (Fig. 2).

**Fig. 2 Fig2:**
[figure not shown]
The Droobi app healthcare provider portal. **a** Portal landing page-dashboard. **b** Chat function amongst healthcare team. **c** Report created by Droobi upon request of educator for physician approval: (i) expanded report view showing glucose monitoring chart and ability to review previous blood glucose readings in chart and table format; (ii) expanded report view showing medication and blood glucose monitoring plan together with diet goals, notes for the team and the assigned healthcare team

The Droobi app has been designed to be simple to use, mimicking existing social media tools. Participant training for use of the app will take place with the educator and technical support team during the initial participant set up phase. The following steps are taken:i.Educate/train participant on app usage;ii.Participants will be subscribed to the app and their profile on the app will be created;iii.Participants will log in their blood glucose readings and communicate with the mobile app team (educators and physician) via the app;iv.Participants will be placed on a diet and lifestyle plan as agreed upon by the participant and healthcare provider team, best suited towards the participant’s needs;v.Throughout the study, participants will receive notifications and advice on how to follow diet and lifestyle changes;vi.Throughout the study; participant interaction and app usage will be tracked.

During the trial, there will be a one-to-one training session with the participant, displaying the mobile application and its key features in the preferred language. Live demonstration on the participant’s phone will be performed, and the participant is instructed to demonstrate application use in the presence of the team to ensure that they are able to use the application easily. The team ensures the participant’s training checklist is completed. Also, a printed manual will be provided, which will also include advice for minimising patient risk (e.g. no app is substitute for medical advice, especially during medical emergencies, and how to use the app and protect privacy). Similar training will be conducted for the educators and physicians involved in the intervention arm.

All training will be carried out by the app development team involved in the study, together with the investigators facilitating interaction. For any technical questions or concerns, all participants (both study participants and healthcare professionals) will have available user support platform during the study duration in addition to a Droobi technical hotline number.

#### Standard care

At baseline, participants will be seen by the dietitian and diabetes educators in the diabetes clinic as part of standard care. The educators contact telephone number, and a diabetes hotline number will be provided to all as standard. The diabetes hotline number is a service provided to patients with diabetes to help communicate with the diabetes educators with questions relating to their diabetes management, medication adjustment such as dose titrations, etc. Appointments thereafter with the educator and/or dietitian will be decided and scheduled according to individual need, with a planned minimum visit every 3 months during the study period.

#### The healthcare provider team

Mobile app intervention team: This team consists of healthcare providers comprising of physician, diabetes educators and dietitians who provide feedback and coaching to participants through the app using all clinical and self-entered information available within the app.

Standard care team: This team consists of healthcare providers comprising of physician, diabetes educators and dietitians providing standard diabetes care based on national and international diabetes guidelines.

Insulin doses were adjusted based on multi-professional assessment to avoid any risks associated with hypoglycaemia.

For the observational comparator population, patients records will be identified via electronic medical records to match inclusion/exclusion criteria of QDMAT participants.

### Criteria for discontinuing or modifying allocated interventions {11b}

Participants may withdraw from the study at any time without their treatment or access to services being affected. Investigators may withdraw participants if they develop a condition that excludes them from the study, e.g. cancer.

### Strategies to improve adherence to interventions {11c}

Participants are contacted in a timely manner to ensure they are reminded of their laboratory investigations and physician's appointments together with the dietitian and educator appointments. Also, the intervention group receive reminders from the healthcare providers on the mobile app. Any difficulties in using the app will be addressed by the healthcare provider and app technical team.

### Relevant concomitant care permitted or prohibited during the trial {11d}

All participants will have access to any required medical care.

### Provisions for post-trial care {30}

Once the intervention completed, the mobile app for the intervention group will be deactivated, and they will be returned to standard diabetes care. In case of injury, care will be provided at HMC without cost, but any outside care will be at the participant’s expense.

### Outcomes {12}

#### Primary outcome

The primary outcome is the difference in mean HbA1c (change from baseline) between the intervention arm and the standard care arm at 6 months based on available resource.

#### Secondary outcomes

Secondary outcomes include differences in:Perceptions of diabetes self-management as assessed by diabetes self-management questionnaire (DSM-Q) [24]; a self-completed questionnaire including 16 items assessing selfcare activities associated with glycaemic control at 0 and 6 months;Attitudes towards disease assessed using the diabetes distress scale (DDS) [25]; a 17-item participant-completed questionnaire assessing psychosocial distress in diabetes at 0 and 6 months;Number of recommended insulin dose adjustments;Number of reported hypoglycaemic events;The time required to reach normoglycaemia;The number of clinical interactions;The proportion of missed clinical appointment;In anthropometric measures (body weight; body mass index [BMI]), blood pressure and lipid profile;Key outcome measures beyond 6 months with follow-up (up to 5 years).

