### Sample size {14}

The initial sample size was based on a clinically relevant difference in HbA1c of 0.5% (5.5 mmol/mol) with SD 1% (11 mmol/mol) between the intervention and the standard care arms [26]. To achieve an 80% power and a significance level of < 0.05, 64 participants would be required in each arm. Assuming a 40% loss to follow-up, 90 participants were planned to be recruited in each arm. However, review of baseline characteristics of recruited participants by the trial steering group identified a higher SD of 1.7% (19 mmol/mol) giving 182 participants per arm, with a total recruitment of 608 participants to include a 40% dropout. Therefore, it was decided to extend recruitment beyond the initially planned number to 608 participants. Sample size calculations were made using STATA 15 MP. For the population cohort comparator group, we aim to select a sample 200 patients identified through the available diabetes registries to examine the impact of trial arms compared to a non-randomised group.

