## Statistical methods

### Statistical methods for primary and secondary outcomes {20a}

Descriptive statistics will be used to summarise and determine the sample characteristics and distribution of patients’ data. The normally distributed data and results will be reported with mean and standard deviation (SD) with corresponding 95% confidence interval (CI); the remaining results will be reported with median and inter-quartile range (IQR). Categorical data will be summarised using frequencies and proportions. Associations between two or more qualitative data variables will be assessed using chi-square (*χ*^2^) test or Fisher exact test, as appropriate. Quantitative data between the two independent groups will be analysed using unpaired *t* or Mann-Whitney *U* test as appropriate.

The analysis will follow the intention to treat principle with last observation carried forward. Difference in mean change from baseline HBA1c between the intervention arm and the standard care arm at 3 and 6 months will be analysed using repeated measure ANOVA method, linear regression and analysis of covariance (ANCOVA) methods as appropriate. Sensitivity analysis will be conducted using other approaches based on data available. Comparisons will be conducted between trial group and the observational cohort using the approaches described above.

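### Reported hypoglycaemic events are to be compared as a raw count with no stated source or time at risk, so the comparison is at risk of ascertainment bias and, if follow-up differs by arm, of exposure bias

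*Protocol article*

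**What the plan says.** All references are to the protocol article.

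- **Outcome.** *Secondary outcomes* lists "Number of reported hypoglycaemic events". It gives no source for the reports and no time at risk.
- **Test.** *Statistical methods {20a}* states: "Quantitative data between the two independent groups will be analysed using unpaired *t* or Mann-Whitney *U* test as appropriate". It adds "The analysis will follow the intention to treat principle with last observation carried forward" and "Sensitivity analysis will be conducted using other approaches based on data available". No rate or exposure term is named.
- **App arm.** *The Droobi app* says that participants log glucose and are alerted when they fail to do so. The provider portal shows "any triggers highlighted (i.e. low or high blood glucose entries", so that staff can set priorities.
- **Both arms.** *Standard care* gives everyone the educator's telephone number and a diabetes hotline. Educator and dietitian appointments follow individual need, "with a planned minimum visit every 3 months during the study period".
- **Data source.** *Plans for assessment and collection of outcomes {18a}* says that data come mostly from electronic medical records and are copied to the case report form. It does not say whether a low reading entered in the app counts as a reported event.
- **Loss.** *Sample size {14}* plans "with a total recruitment of 608 participants to include a 40% dropout", with no split by arm.
- **Blinding.** *Who will be blinded {17a}*: participants and the team delivering the intervention know the allocation.

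**The concern.** A count of reported events depends on three things: how often hypoglycaemia occurs, how likely an event is to be noticed and recorded, and how long the person is observed. Randomisation balances the underlying risk at baseline. It does not balance the other two.

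Noticing and recording differ by design, because prompted logging and automatic flagging of low entries exist in one arm only. Length of observation will vary a good deal if 40% are lost, and the stated tests ignore it. Last observation carried forward does not help: carrying a running total forward amounts to counting no events after departure, which returns the raw count.

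The comparison could therefore show an excess with the app that only reflects better detection. It could also hide or exaggerate a real difference if one arm is observed for longer. The exclusion criteria show that the investigators take hypoglycaemia seriously as a risk, so readers will look at this result.

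**Working it through.** **The plan's own figure.** It concerns HbA1c only; nothing is stated for hypoglycaemia. With a difference of 0.5 and SD 1.7, two-sided 5% and 80% power:

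n per arm = 2 × (1.960 + 0.842)² × 1.7² / 0.5² = 181.5, so 182. Then 182 / 0.6 = 303.3, so 304 per arm and 608 in total. This reproduces.

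**Inputs for the check.** From the protocol: 304 per arm, 6 months of intervention, 40% planned loss. Assumed, because the protocol gives none: 0.25 events per month, between-person dispersion 1 (gamma-Poisson), dropouts leaving uniformly over the 6 months, and the dropout and reporting ratios by arm shown below. True rates are equal in every case, so any rejection is false. Simulation: 2,000 runs, two-sided 0.05.

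**Formula.** Mean exposure = 6 × (1 − d/2) months for dropout d. Expected count ratio (app / control) = reporting ratio × mean exposure in app / mean exposure in control.

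**Exposure alone (reporting ratio 1).**

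| Dropout app / control | Mean months | Count ratio | Rejection, t | Rejection, Mann-Whitney | Person-time rate ratio |
|---|---|---|---|---|---|
| 40% / 40% | 4.8 / 4.8 | 1.00 | 5% | 5% | 1.00 |
| 30% / 50% | 5.1 / 4.5 | 1.13 | 19% | 21% | 1.00 |
| 50% / 30% | 4.5 / 5.1 | 0.88 | 19% | 21% | 1.00 |
| 20% / 60% | 5.4 / 4.2 | 1.29 | 58% | 66% | 1.00 |

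Ignoring exposure does no harm to the type I error when dropout is equal. It matters when dropout is not, and dividing by person-time then removes the bias.

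**Reporting alone (dropout 40% in both arms).**

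| Reporting ratio | Count ratio | Rejection, t | Rejection, Mann-Whitney | Person-time rate ratio |
|---|---|---|---|---|
| 1.25 | 1.25 | 49% | 38% | 1.26 |
| 1.5 | 1.5 | 94% | 85% | 1.50 |
| 2.0 | 2.0 | 100% | 100% | 2.00 |

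Here the person-time rate does nothing; the reporting ratio passes straight through.

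**Second check, with a negative binomial test.** Take n = 182 per arm, 2 true events per person in both arms and dispersion a = 1. The reported mean m is 2 × the fraction captured. SE(log RR) = √[(1/m₁ + a)/n + (1/m₀ + a)/n] and z = log RR / SE.

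- Capture 80% v 50%: m = 1.6 and 1.0, RR 1.60, SE 0.141, z 3.33, rejection 91%.
- Capture 90% v 70%: m = 1.8 and 1.4, RR 1.29, SE 0.134, z 1.87, rejection 47%.
- Capture 80% v 70%: m = 1.6 and 1.4, RR 1.14, SE 0.135, z 0.99, rejection 17%.

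These capture fractions are assumptions too. The result confirms that a proper count model, on its own, does not cure unequal capture.

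**The case against.** The best defence is that this is one of many secondary outcomes in an article that condenses a longer protocol. The sentence on tests is generic and says that the choice will be made as appropriate. An event definition or count model may stand in the full protocol or the analysis plan, and the schedule of assessments, which is not visible here, may already hold a common question on hypoglycaemia. That tempers the criticism of the test. It does not dispose of the point: the article does state the outcome as a raw reported count and does name tests for such data, and a later choice of model cannot equalise how events came to be recorded.

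A reader might infer more than the text supports in four places:

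- **That controls have no continuous way to report.** The hotline and educator number go to all participants, and 3-monthly visits are a minimum. What controls lack is alerted logging and flags. The alert, moreover, is for missed entries, not for low readings.
- **That the comparison is certainly biased.** Outcome data come mostly from medical records, and the protocol leaves open whether app entries feed the count. Even if they do not, staff alerted by a flag may record events that would go unrecorded in controls; that is a risk, not a demonstrated bias.
- **That the planned 40% loss by itself distorts the counts.** It does so only if follow-up differs by arm, and no figure by arm is given.
- **That this is the trial's main harm comparison.** No section calls it that, and adverse events are recorded separately throughout.

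**Conclusion.** The point holds as a risk of bias in a secondary outcome; it does not touch the HbA1c analysis. The ascertainment part is the more important. Its likely direction is more apparent events in the app arm, its size is unknown, and whatever ratio exists enters the estimate undiminished. Across assumed ratios of 1.25 to 2.0, a false difference is declared in 38% to 100% of trials with the stated tests.

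The exposure part is conditional. Dropout ten points either side of 40% gives a count ratio of about 1.13 or 0.88 and a type I error near 20%; equal dropout gives about 5%. These rejection figures depend on the assumed event rate, dispersion and uniform exit times, and should be read as illustrations.

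**What to change.** 1. State what counts as a reported event and from which sources. For the between-arm test, use only events obtained from sources common to both arms (visit reports and the medical record), and exclude events known only from app entries.
2. Tabulate app-logged low readings for the app arm separately, without a test.
3. Analyse the common-source events as a rate, for example by negative binomial regression with log follow-up time as offset, adjusted for the minimisation factors (age band, gender, diabetes duration, insulin regimen). Define follow-up time in the same way in both arms, drop last observation carried forward for this outcome, and report follow-up by arm.
4. Use the same offset for the counts of dose adjustments and clinical interactions. Only the exposure issue is carried over to these; the app is meant to change them, so a difference in the counts is not in itself an artefact.

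The cost is mainly analysis wording, plus marking the source of each event on the case report form. A new common question at visits would help, but may come too late because recruitment was due to end about May 2021; the restriction to common sources does not depend on it.

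The downside is that app-only events leave the formal comparison. Some difference in recall and in staff recording may also remain because the trial is open label, and the offset assumes that people who leave would have had events at a similar rate had they stayed. The report should say so.
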